### Products tested: electronic cigarette

The e-cigarette will be used in this study. It is a disposable model that closely resembles the shape of a tobacco cigarette. Its heating element in the atomizer is activated by a rechargeable 3.7-V, 120mAh, lithium-ion battery. Standard performance guarantees the equivalent of 300 to 400 puffs/each disposable product. The e-cigarette contains a liquid solution of vegetable glycerin in which nicotine or an aroma is dissolved. Two different types of disposable e-cigarette will be provided for the study; high-nicotine (with 24 mg nicotine) and no-nicotine (with a tobacco aroma). Detailed toxicology and nicotine content analyses of the e-cigarette has been provided to the local ethics review boards (ERBs) (Figure 1).

**Figure 1 F1:**
[figure not shown]
**Electronic cigarette.** It is a disposable model that closely resembles the shape of a tobacco cigarette, with a rechargeable 3.7-V, 120mAh, lithium-ion battery. The electronic cigarette contains a liquid solution of vegetable glycerin in which nicotine or an aroma is dissolved.

### Products tested: the PAIPO nicotine-free inhalator (EchosSrl, Milan, Italy)

This plastic device resembles a cigarette and is intended to replace some of the rituals associated with smoking gestures, for example, the hand-to-mouth action of smoking, and handling and manipulation of cigarettes. The plastic device contains a sponge filter soaked in natural oil enriched with extracts of different aromas. For this study protocol we will provide a placebo grapefruit-flavor PAIPO inhalator (Figure 2).

**Figure 2 F2:**
[figure not shown]
**The PAIPO nicotine-free inhalator (EchosSrl, Milan, Italy).** It is a plastic device that resembles a cigarette and is intended to replace some of the rituals associated with smoking gestures. The plastic device contains a sponge filter soaked in natural oil enriched with extracts of different aromas.

### Study design

The study is a three-arm, randomized controlled, clinical trial designed to assess the efficacy and safety of the e-cigarette with 24 mg nicotine, the e-cigarette with no nicotine, and the PAIPO nicotine-free inhalator. We adhered to Consolidated Standards of Reporting Trials (CONSORT) guidelines in the design of the trial.

At screening the diagnosis of schizophrenia will be determined using the structured clinical interview for DSM-IV axis I disorders - clinical version (SCID-I-CV); subjects with organic psychosis, learning disabilities or requiring a translator because of lack of Italian fluency will be excluded from the study. The psychopathological status of the participants will be assessed by a trained psychiatrist (blinded to the treatment conditions) using the positive and negative syndrome scale (PANSS) to evaluate the severity of illness. Written informed consent will be obtained by all eligible participants at this visit. Screening in brief is as follows: informed consent; inclusion/exclusion criteria; Case Report Form”CRF (socio-demographic factors; smoking history; SCID-I-CV; PANSS); if eligible book next appointment in 1 week.

At baseline (BL), participants will be randomized into three separate study groups. The randomization sequence will be computer generated by permuted blocks of five for each of the three study conditions (A, B, and C). Participants randomized in study group A will receive a 12-week supply of the e-cigarette with 24 mg of nicotine; those in study group B, a 12-week supply of the e-cigarette 0 mg of nicotine; participants in study group C will receive a 12-week supply of the PAIPO nicotine-free inhalator. A prospective evaluation of efficacy and safety will be repeated at an additional follow-up visit at 24 weeks. The study will consist of a total of seven visits: a screening visit, a BL visit and five follow-up visits (at weeks 4, 8, 12, 24, and 52). Three telephone contacts (TC) will be scheduled during the treatment phase (at weeks 2, 6, and 10) (Figure 3).

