## Methods

### Participants

One hundred fifty-three schizophrenic regular smokers will be recruited in three centers (Smoking Cessation Centre University of Catania Medical Hospital; Psychiatric Unit of University of Catania Medical Hospital; CTA “Villa Chiara” Psychiatric Clinic) following placement of advertisements in local newspapers and radio/television network inviting them to try the e-cigarette to reduce the risk of tobacco smoking. Each participating center will include 51 eligible smokers in the study. The study protocol has been approved by the Ethical Committee of the University of Catania (Record number 674; 30-05-2013) in accordance with the Helsinki Declaration. Written informed consent will be obtained by all participants.

Inclusion criteria are: 1) schizophrenic subjects (according to DSM-IV-TR criteria) from Sicily (Italy), who smoke tobacco cigarettes, in who are in the stable phase of illness (no relapse/hospitalization and/or need to change psychopharmacological treatment in the last 12 months); 2) smoked ≥10 factory-made cigarettes/day for at least the past five years; 3) age 18 to 65 years; 4) in good general health (absence of cancer, acute myocardial infarction, unstable angina, severe cardiac arrhythmia, recent cerebrovascular incident, or severe atherosclerosis); 5) not currently attempting to quit smoking or wishing to do so in the next (a specific test will be included to check their unwillingness to quit) 6 months; 6) committed to follow the trial procedures.

Exclusion criteria are: 1) use of smokeless tobacco or nicotine replacement therapy; 2) pregnancy or breastfeeding; 3) current or recent (less than 1 year) history of alcohol and/or drug abuse; 4) other significant comorbidities according to the Investigator’s clinical assessment (for example, cancer, acute myocardial infarction, unstable angina, severe cardiac arrhythmia, recent cerebrovascular incident, or severe atherosclerosis.

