### Sample size

All statistical tests were two-tailed and were considered to be statistically significant at *P* < 0.05. A sample size of 133 subjects was calculated accepting the following parameters: effect size medium = 0.30; alpha = 0.05; 1-ß = 0.80. Considering a drop-out rate of 15%, a total sample size of 153 smokers was determined. The smokers will be randomized into the three arms of our study protocol (51 smokers for each arm).

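### The blocking rule is ambiguous: a literal block of five cannot be balanced over three equal arms, no reading guarantees 51 per arm, and one fixed published block size makes some allocations predictable

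*Protocol article*

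**What the plan says.** Under Study design, the protocol article says that "participants will be randomized into three separate study groups" at baseline, and gives the method: "The randomization sequence will be computer generated by permuted blocks of five for each of the three study conditions (A, B, and C"). It mentions no unequal allocation ratio and no rule for filling a block.

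Under Sample size it gives the intended result: "The smokers will be randomized into the three arms of our study protocol (51 smokers for each arm").

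Under Participants it says "One hundred fifty-three schizophrenic regular smokers will be recruited in three centers" and "Each participating center will include 51 eligible smokers in the study".

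The article does not say whether there is one list or one list per centre. The two product sections describe a battery-powered e-cigarette (arms A and B) and a plastic inhalator with an oil-soaked sponge (arm C). The only blinding mentioned is that of the psychiatrist who rates the PANSS.

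**The concern.** The method and the intended result do not fit together as written. Five is not a multiple of three, so a block of five must give at least one arm fewer places than another. Whoever programs the list has to choose a rule that the text does not supply, and the choice can decide whether the arms come out nearly equal or one arm ends at half the size of the others.

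The sentence can also mean five places for each arm, that is, a block of 15. That block is balanced, but a reader cannot tell which is meant.

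A second issue holds on both readings. The block size is fixed and now public, and product C can be told from A and B on sight. Staff who follow the allocations can sometimes know whether the next participant will receive C. That weakens allocation concealment, which matters when those staff also decide whom to enrol and when.

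**Working it through.** **The plan's own figures.** The Sample size section says: "A sample size of 133 subjects was calculated accepting the following parameters: effect size medium = 0.30; alpha = 0.05; 1-ß = 0.80". A chi-square test with w = 0.30, alpha 0.05, power 0.80 and 4 degrees of freedom (three arms by three outcome classes) gives 133 exactly. It continues: "Considering a drop-out rate of 15%, a total sample size of 153 smokers was determined". 133 × 1.15 = 152.95, rounded up to 153, and 153 / 3 = 51. So the target is 1:1:1, and blocking does not enter the calculation.

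**Divisibility.** Inputs: 3 arms, 153 in total, 51 per centre.

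- Block of 5: 5 = 3 × 1 + 2, so no block is 1:1:1. 153 / 5 = 30.6 and 51 / 5 = 10.2.
- Block of 15 (five per arm): each block is 5:5:5. 153 / 15 = 10.2 and 51 / 15 = 3.4.
- Block of 3, for comparison: 153 / 3 = 51 and 51 / 3 = 17, both whole.

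**Arm totals for a list of 153.** The filling rules for a block of five are assumptions, since the article gives none.

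- *Five, fixed 2:2:1.* 30 blocks give 60/60/30. The last three participants add on average 1.2, 1.2 and 0.6, so about 61/61/31. Exactly 51/51/51 is impossible.
- *Five, short arm drawn at random in each block* (200,000 simulated lists). Exact balance in 2.6%; mean difference between largest and smallest arm 5.5; 95th percentile 11.
- *Five, short arm rotated.* Three blocks give 5/5/5, so 30 blocks give 50/50/50. The last three come from a 2:2:1 block, and the arms end at 50 to 52. Exact balance: (2 × 2 × 1) / C(5,3) = 4 / 10 = 40%.
- *Fifteen, one list.* 10 blocks give 50/50/50. The last three come from a 5:5:5 block, and the arms end at 50 to 53. Exact balance: 5³ / C(15,3) = 125 / 455 = 27.5%.
- *Fifteen, separate list per centre* (simulated). Each centre is 3 blocks plus 6 participants. Exact balance overall in 7.0%; mean difference 3.3; 95th percentile 6.

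**What the worst case costs.** With equal variance per participant, the variance of the A versus C difference at 61 and 31, relative to 51 and 51, is (1/61 + 1/31) / (2/51) = 0.04865 / 0.03922 = 1.24, an increase of about 24%. At 50 and 53 it is (1/50 + 1/53) / (2/51) = 0.03887 / 0.03922 = 0.99, which is no loss.

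**Predictability of C versus not-C.** Assumption: the observer knows the block size, knows where blocks start and sees every earlier allocation. An allocation is certain when only one type of place remains in the block.

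- *Five, 2:2:1 with C short.* The places left after C number (4 + 3 + 2 + 1 + 0) / 5 = 2 on average. A C in last place adds 1/5 = 0.2. Total 2.2 of 5, or 44%.
- *Fifteen, five per arm.* The expected closing run of not-C is 10 / 6 = 1.67 and of C is 5 / 11 = 0.45. Total 2.12 of 15, or 14%.
- *Three, fixed and known.* 2 / 2 + 1 / 3 = 1.33 of 3, or 44%. A short block is therefore safe only if the size varies and sites do not know it.

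**The case against.** The strongest reply is that five per arm is the natural reading. It is the only one that gives balanced blocks without an added rule, and it agrees with the 51 per arm stated elsewhere. On a single list no arm is then more than two from target, and a cut last block is ordinary. A planned 51 need not be met exactly. All of this stands, and it is why the point is not severe. It does not settle the matter, because the sentence does not state the total block size, and the literal alternative reaches 61/61/31 under one filling rule. Brevity in a journal article is no excuse here: the block size is given, but unclearly.

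The predictability figures are upper values. With one list shared by three centres, a site sees only part of the sequence and can infer less.

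A reader might go further in three ways that the document does not support.

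- *That the list is not stratified by centre, so that device is confounded with setting.* The article is silent on stratification, and a condensed article may leave this to the full protocol. The 51 per centre fits centre lists, and the Study schedule section places visits at the smoking cessation clinic.
- *That the sample size assumes balance within centre.* The Sample size section does not mention centre, and 133 and 153 reproduce without it.
- *That a definite amount of power is lost.* The article gives an effect size of 0.30 but no responder rates by arm. A loss in percentage points would rest on rates supplied from outside, and would apply only to the fixed 2:2:1 rule, which the article does not describe.

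**Conclusion.** The point holds as a badly fixed rule of moderate to minor weight. Read literally, the block of five is incompatible with equal allocation, and the result depends on an unstated rule: from 50 to 52 per arm at best to about 61/61/31 at worst. Read as a block of 15, the size imbalance is trivial (50 to 53 per arm on one list), but the blocks still close at neither 153 nor 51. So no reading guarantees 51 per arm. It does not follow that 51 per arm cannot occur, or that the trial will be materially unbalanced.

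The concealment issue remains on both readings. With a fixed, known block size, up to about 14% (block of 15) or 44% (fixed 2:2:1 block with C short) of allocations are certain as to C or not-C, assuming that staff see all earlier allocations. The planned sample size is not affected.

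**What to change.** Replace the sentence under Study design with, for example: *The sequence will be computer generated in permuted blocks of randomly varying size (3, 6 or 9, with equal numbers of A, B and C in each block); block sizes will not be disclosed to sites, and the list will close at 51 per arm.* If lists are kept by centre, add that each closes at 17 per arm.

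This is feasible. Three blocks of 9, three of 6 and two of 3 make 27 + 18 + 6 = 51 for one centre, and three times that set makes 153. If recruitment stops inside a block, the arms differ by at most three per list.

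The cost is one sentence and a list generated under the new rule, with no extra patients and no change to the sample size. It must be done before the first randomization, and the Trial status section indicates that recruitment had not begun. If a list already exists and used blocks of 15, saying so would remove the ambiguity; the varying, undisclosed sizes would still be preferable for concealment.

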**Figure 3 F3:**
[figure not shown]
**Study design.** The study is a three-arm, randomized controlled, clinical trial designed to assess the efficacy and safety of the e-cigarette with 24 mg nicotine, the e-cigarette with no (0 mg) nicotine and the PAIPO nicotine-free inhalator.

### Study schedule

Participants will attend their study visits at the smoking cessation clinic at approximately the same time of day. With the exception of the BL study day, most visits will take approximately 10 to 15 minutes to complete. The BL visit will be carried out within seven days of the screening visit. At BL (study visit 1), socio-demographic factors, and detailed smoking history will be annotated and individual pack-years (pack/yrs) calculated, together with the ratings of quality of life and neurocognitive functioning assessed by the quality of life scale (QLS) and brief assessment of cognition in schizophrenia (BACS), respectively. Physical cigarette dependence and behavioral dependence will be measured with the Fagerstrom test for cigarette dependence (FTCD) and Glover-Nilsson smoking behavioral questionnaire (GN-SBQ), respectively. Additionally, levels of carbon monoxide in exhaled breath (eCO) will be measured using a portable device (Micro CO, Micro Medical Ltd, Kent, UK). Vital signs (heart rate (HR) and blood pressure (BP)), body weight, spirometry, and AEs will also be recorded at baseline.

Participants will be given a free supply of e-cigarettes or PAIPO inhalators (on average, a 4-week supply of e-cigarettes) and instructed on how to correctly use them. Key trouble-shooting support will be provided and phone numbers will be supplied for medical assistance. A full 4-week supply of nicotine or no-nicotine e-cigarettes, or PAIPO inhalators (depending on the study-arm allocation) will be also provided so that every participant will have enough disposable products for each study period; a study diary recording will be used to check for the most common AEs related to the use of e-cigarettes (for example, dry cough, mouth irritation, throat irritation, headache, shortness of breath, nausea et cetera). No emphasis on encouragement, motivation and reward for the smoking cessation effort will be provided, because this study was intended to monitor schizophrenic smokers who are unwilling to quit. Participants will be instructed to return every four weeks to obtain their 4-weekly supply of e-cigarettes or PAIPO inhalators.

The BL (visit 1) in brief is as follows: CRF (physical examination, FTCD, GN-SBQ, QLS, BACS, HR, BP, weight, eCO, spirometry, AEs); craving/visual analog scale (VAS); MNWS; randomization into either study group A (e-cigarette 24 mg), B (e-cigarette 0 mg), or C (PAIPO); dispense 4-weeks supply of nicotine e-cigarette, no-nicotine e-cigarette or PAIPO inhalator (depending on the study-arm allocation); dispense 4-week study diary for AEs; book for next appointment in 4 weeks (week 4; study visit 2).

By and large, at week 4 (study visit 2), and week 8 (study visit 3), participants will a) receive further study diaries for the residual study periods; b) have their eCO levels and vital signs recorded; and c) return their completed study diaries and used study products. At the end of the week-12 study visit, no more products will be provided by the investigators.

Week-4 (visit 2) in brief is as follows: collect 4-week study diary for AEs; CRF (number of cigarettes/day, eCO, HR, BP); craving/VAS; MNWS; PANSS; smokers’ product preference survey; dispense next 4-week supply of nicotine e-cigarette, no-nicotine e-cigarette or PAIPO inhalator (depending on the study-arm allocation); dispense next 4-week study diary for AEs; book for next appointment in 4 weeks (week 8; study visit 3).

Week-8 and -12 (visits 3 and 4) in brief are as follows: collect 4-week study diary for AEs; CRF (number of cigarettes/day, eCO, HR, BP); craving/VAS; MNWS; PANSS; smokers’ product preference survey; dispense next 4-week supply of nicotine e-cigarette, no-nicotine e-cigarette or PAIPO inhalator (depending on the study-arm allocation); book for next appointment in 12 weeks (week24; study visit 5).

Week 24 (visit 5) in brief is as follows: collect 4-week study diary for AEs; CRF (number of cigarettes/day, eCO, HR, BP); craving/VAS; MNWS; PANSS; BACS; QLS; smokers’ product preference survey; spirometry; book for next appointment for the final visit (week 52; study visit 6).

Week 52 (visit 6) in brief is as follows: CRF (number of cigarettes/day, eCO, HR, BP); craving/VAS; MNWS; PANSS; BACS; QLS; smokers’ product preference survey; spirometry.

Study participants will attend a final follow-up visit at week 52 to report product use and the number of any tobacco cigarettes smoked (from which reduction and quit rates could be calculated), and to re-check eCO levels. Quality of life, neurocognitive functioning and psychopathological status will be assessed by QLS, BACS, and PANSS, respectively. Vital signs (HR and BP), body weight, and spirometry will be recorded again as well as participants’ perceptions of the specific product they are using [11].

Early termination visit (unscheduled visit) is as follows: CRF (number of cigarettes/day, eCO, HR, BP); craving/VAS; MNWS; PANSS; BACS; QLS; smokers’ product preference survey; spirometry (Table 1).

**Table 1 T1:** Study schedule

**Procedure**		**BL Visit**	**Wk4**	**Wk8**	**Wk12**	**Wk24**	**Wk52**	**Early termination visit**
		**Visit 1**	**Visit 2**	**Visit 3**	**Visit 4**	**Visit 5**	**Visit 6**	
Informed consent		**X**						
Inclusion/exclusion criteria (review)		**X**						
**CRF**	Sociodemografic factors	**X**						
	Smoking Hx	**X**						
	no. cig/day	**X**	**X**	**X**	**X**	**X**	**X**	**X**
	Physical examination	**X**					**X**	
	FTDC, GN-SBQ, QLS, BACS	**X**			**X**	**X**	**X**	**X**
	eCO	**X**	**X**	**X**	**X**	**X**	**X**	**X**
	HR, BP	**X**	**X**	**X**	**X**	**X**	**X**	**X**
	Weight	**X**				**X**	**X**	
	AEs	**X**	**X**	**X**	**X**	**X**	**X**	**X**
Randomization into either study group A (Ecig 24 mg), B (Ecig o mg), or C (paipo)		**X**						
Dispense 4-weeks supply of either nicotine or no-nicotine or paipo (depending on arm allocation)		**X**	**X**	**X**	**X (x3)**			
Dispense 4-weeks’ study diary for AEs		**X**	**X**	**X**	**X (x3)**			
Spirometry		**X**			**X**	**X**	**X**	**X**
Book for next appointment in 4 weeks (week-4; study visit 2)		**X**	**X**	**X**	**X (x3)**	**X(x6)**		
Craving/VAS		**X**	**X**	**X**	**X**	**X**	**X**	**X**
MNWS		**X**	**X**	**X**	**X**	**X**	**X**	**X**
PANSS			**X**	**X**	**X**	**X**	**X**	**X**

### Study outcome measures

A reduction ≥50% in the number of cigarettes/day from BL, defined as self-reported reduction in the number of cigarettes/day (≥50%) compared to BL (together with an eCO levels reduction, to objectively document a reduction from baseline), will be calculated at each study visit (referred to as reducers). Abstinence from smoking, defined as complete self-reported abstinence from tobacco smoking - not even a puff (together with an eCO concentration ≤7 ppm), will be calculated at each study visit (referred to as quitters). Smokers who do not satisfy the criteria of reducers or quitters will be defined non responders. Smokers who leave the study protocol before its completion due to lack of efficacy or poor tolerability of the product under investigation, will carry out the early termination visit and will be defined as non responders.

AEs, symptoms thought to be related to tobacco smoking and e-cigarette use, and to withdrawal from nicotine, will be annotated at BL and at each subsequent study visit on the AE page of the study diary. Vital signs will be also recorded. The number and the percentage of subjects experiencing AEs, adverse reactions, serious AEs and AEs leading to study withdrawal will be summarized by treatment group. AEs will also be summarized by system organ class and preferred term using the *MedDRA* dictionary.

Quality of life, neurocognitive functioning and psychopathological status will be reassessed by QLS, BACS and PANSS, respectively. Participants’ perceptions and liking of the product will be assessed by asking them to rate their levels of satisfaction with the products compared to their own cigarettes using a VAS, scoring from 0 to 10 points (0 = completely unsatisfied, 10 = fully satisfied). Using the same scale, they will also rate how much they miss their own brand (0 = did not miss it at all, 10 = missed it too much) and whether they would recommend it to a friend/relative (0 = not recommended at all, 10 = absolutely recommended).

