Healthcare providers previously have not offered tobacco dependence treatment to patients with schizophrenia, probably secondarily to stigma or lack of information [23]. Moreover, smokers with schizophrenia have a more severe nicotine dependence compared to smokers without schizophrenia [14]. Hence, interventions may not be as effective as they have been shown to be in the general population. We also need to consider the safety of these interventions, particularly in relation to drug therapy. In addition, nicotine withdrawal can cause symptoms such as depression, anxiety and irritability. All these factors may contribute to changes in the mental state of these patients, and the extent of these changes remains unclear [24]. For these reasons, recent initiatives have aimed to study smoking habits and specific intervention programs for smokers with schizophrenia [7,8,15,24].

The proposed randomized trial consists of an investigation of the efficacy and safety of e-cigarettes in schizophrenic smokers. To date there are no large randomized trials of e-cigarettes in schizophrenic smokers. The main strengths of the SCARIS study are the following: it is the first large RCT on schizophrenic patients, involving inpatients and outpatients, with a three-arm study design and long-term follow up (52 weeks).

The goal is to propose an effective intervention to reduce the risk of tobacco smoking, as a complementary tool to treat smokers with schizophrenia. Therefore, as our clinical experience in the smoking cessation/reduction treatment of smokers suffering of schizophrenia evolves, the smoking cessation and reduction in schizophrenia (SCARIS) study protocol stands as a unique milestone robust trial, which will contribute to our fundamental understanding of the role of the e-cigarette in smoking cessation/reduction and its influence on the health status of this particular population.

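### Adverse event recording is worded around suspected cause and names e-cigarettes but not the PAIPO comparator, which conflicts with the planned separate summaries of AEs and adverse reactions and risks uneven recording between arms

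*Protocol article*

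**What the plan says.** The protocol article puts safety in its primary objective and lists AEs there (Objectives, Primary). AEs appear again among the secondary outcomes.

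Four statements govern how AEs are collected and reported:

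- **Recording rule (Study outcome measures):** "AEs, symptoms thought to be related to tobacco smoking and e-cigarette use, and to withdrawal from nicotine, will be annotated at BL" and at each later visit, on the AE page of the diary.
- **Instrument (Study schedule):** "a study diary recording will be used to check for the most common AEs related to the use of e-cigarettes". The examples given are local and general symptoms such as cough, throat irritation, headache and nausea.
- **Reporting (Study outcome measures):** "The number and the percentage of subjects experiencing AEs, adverse reactions, serious AEs and AEs leading to study withdrawal will be summarized by treatment group".
- **Coding (same section):** "AEs will also be summarized by system organ class and preferred term", using MedDRA.

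Table 1 has an AE row, without any relatedness qualifier, at every visit and at early termination. The comparator in group C is the PAIPO inhalator, which is not an e-cigarette. Neither the recording rule nor the diary sentence mentions it.

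Psychiatric status is followed separately: "Quality of life, neurocognitive functioning and psychopathological status will be reassessed by QLS, BACS and PANSS, respectively".

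**The concern.** An AE is normally recorded first and judged for relatedness second. Here the natural reading of the recording rule reverses that order: what is annotated is what someone already thinks is due to smoking, e-cigarette use or nicotine withdrawal. Two consequences would follow.

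1. **Comparison between arms.** The product named in the rule is the product of groups A and B only. A symptom that a group C participant attributes to PAIPO has no product category, and PAIPO is visibly a different device. If recording depends on attribution, the arms can differ in recorded AEs when they do not differ in true AEs.
2. **Psychiatric events.** The Discussion says of treatment safety and nicotine withdrawal in these patients: "All these factors may contribute to changes in the mental state of these patients". Entry requires 12 months without relapse, hospitalization or need to change psychopharmacological treatment (Participants). A relapse during follow-up that staff put down to the illness itself would fall outside the recording rule in all three arms.

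**Working it through.** **No figure in the plan is contested.** The check is mainly a comparison of text, followed by an illustration on assumed inputs.

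**Step 1: definition or list?** The sentence can be read as a definition (AEs, that is, symptoms thought related to the three causes) or as a list (AEs, plus such symptoms, plus withdrawal symptoms). The grammar favours the definition. No conjunction joins AEs to symptoms, and the phrase about withdrawal continues the earlier *related to*. The diary sentence in Study schedule, which ties AEs to e-cigarette use, points the same way. Nowhere does the article say that events are recorded regardless of cause.

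**Step 2: recording against reporting.** The reporting sentence treats AEs and adverse reactions as different counts. Adverse reactions are the related subset of AEs. If only symptoms thought related are recorded, the two counts largely coincide. MedDRA coding and the serious-AE summary cannot restore what was never recorded.

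**Step 3: coverage by arm under the literal reading.**

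| Suspected cause | A (24 mg) | B (0 mg) | C (PAIPO) |
|---|---|---|---|
| Tobacco smoking | covered | covered | covered |
| Nicotine withdrawal | covered | covered | covered |
| Assigned product | covered | covered | not named |
| Underlying illness or other | not covered | not covered | not covered |

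The asymmetry is confined to the third row. The psychiatric gap is the fourth row and affects all arms alike.

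**Step 4: what else captures events over time.** PANSS is scheduled at weeks 4, 8, 12, 24 and 52 and at early termination. The gaps after week 12 are 24 − 12 = 12 weeks and 52 − 24 = 28 weeks. The last diaries in Table 1 are three 4-week diaries at week 12, which reach week 12 + 3 × 4 = 24. The visit-by-visit text for week 52 lists neither a diary nor AEs, although Table 1 marks AEs at that visit. An event that begins and resolves between weeks 24 and 52 is therefore the least protected.

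**Step 5: illustration only.** All risks and recorded fractions below are assumptions; the documents give none. Recorded rate = true risk × probability that an event is attributed and so recorded.

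- True risk 20% in both arms, recorded 80% in A and 40% in C: 0.20 × 0.80 = 16% against 0.20 × 0.40 = 8%, a spurious risk ratio of 2.0.
- Recorded 60% and 50%: 12% against 10%, ratio 1.2.

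Now assume that an e-cigarette arm records all its events and PAIPO a fraction s, with 51 per arm (Sample size). Let p1 = p, p2 = s·p and p̄ = (p1 + p2)/2. The chance of a two-sided result at 0.05 is about Φ[(p1 − p2 − 1.96·SE0)/SE1], where SE0 = √(p̄(1 − p̄)·2/51) and SE1 = √((p1(1 − p1) + p2(1 − p2))/51).

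Example with p = 0.20, s = 0.50: SE0 = √(0.15 × 0.85 × 2/51) = 0.0707; SE1 = √((0.16 + 0.09)/51) = 0.0700; Φ[(0.10 − 0.1386)/0.0700] = 0.29.

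| True risk, both arms | s = 0.75 | s = 0.50 | s = 0.25 |
|---|---|---|---|
| 10% | 2.5 points; 0.065 | 5 points; 0.157 | 7.5 points; 0.345 |
| 20% | 5 points; 0.097 | 10 points; 0.291 | 15 points; 0.633 |
| 40% | 10 points; 0.182 | 20 points; 0.599 | 30 points; 0.950 |

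Each cell gives the spurious difference and the approximate chance of a significant result when the true risks are equal. The formula is a normal approximation without the Yates correction and is rough where few events are expected. The range runs from negligible to decisive, so the table shows sensitivity to the recording gap, not a forecast.

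**The case against.** The strongest reply is that the surrounding text points to wider collection. The sentence can be read as a list. Separate summaries of AEs and adverse reactions make sense only if unrelated events are collected too. Table 1 carries a plain AE row at every visit. The same symptoms are annotated at baseline, before any product is used, which suits a set of symptom types better than a case-by-case judgement of cause. And this is a condensed article, so event lists and serious-AE procedures may sit in the full protocol.

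Much of this stands, and it limits the point to one about wording. It does not remove it. The wider intent has to be inferred, while the two sentences that tell staff and participants what to write down both point to suspected cause. Even on the list reading, the product-related item names e-cigarettes only. This is stated text that can be followed literally, not detail left out for brevity.

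Three stronger inferences are not supported:

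- **That group C is under-recorded.** Its participants smoke tobacco, so their smoking and withdrawal symptoms are covered, and the diary is dispensed without distinction by arm. Under-recording is possible, not shown.
- **That psychiatric deterioration goes unmeasured.** PANSS is repeated at every follow-up visit and at early termination, and withdrawal is rated by MNWS at every visit from baseline. A score is not an AE record, but the trial is not blind to mental state.
- **That the authors themselves name relapse, admission or medication change as the safety concern.** The Background speaks of worsening psychiatric symptoms and suicidal ideation, and the Discussion of withdrawal symptoms and altered mental state. Relapse, hospitalization and treatment change appear as entry criteria only.

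**Conclusion.** The point holds as a defect of wording in a trial whose primary objective includes safety. Read literally, the recording rule and the diary description place the judgement of relatedness before recording, leave out the comparator product, and conflict with the planned distinction between AEs and adverse reactions.

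The consequence is a risk of arm-dependent recording. Its likely direction is against the e-cigarettes, because their symptoms are the ones prompted for. Separately, psychiatric events judged unrelated may be missing from the AE counts in every arm, which would understate absolute risk throughout. That exposure is greatest after week 12, when visits are 12 and then 28 weeks apart.

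The size of any bias cannot be estimated from the documents; it depends entirely on a recording gap that they do not quantify. The conclusion rests on taking the sentence as a definition, which is the more natural reading but not the only one. If the full protocol already requires all events to be recorded regardless of cause, the remaining task is to bring these two sections into line with it.

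**What to change.** Reword the AE sentence in Study outcome measures and the diary sentence in Study schedule so that they agree:

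1. Record every untoward event from baseline to week 52 in all three arms, regardless of suspected cause.
2. State that this includes psychiatric relapse, psychiatric hospitalization and change of psychopharmacological treatment. This concerns recording only, not management.
3. Use one product-neutral diary and checklist in groups A, B and C.
4. Assess relatedness to the assigned product afterwards, as a separate field, and derive adverse reactions from it.
5. Make the visit lists match the AE row of Table 1, so that events in the interval from week 24 to week 52 are asked for at the final visit.

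The cost is a change of protocol and diary wording, slightly more AE entries and some extra coding. No new visits or procedures are needed. Headline AE rates will be higher, because unrelated events will now be counted.
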